#### **5.5.4 Randomisation and Preparation of Study Drug**

Randomisation will be administered centrally via the Bristol Randomised Trials Collaboration (BRTC) Clinical Trials Unit (CTU) after the inclusion/exclusion criteria have been confirmed and the post-surgery randomisation criteria are met as confirmed by the PI. Eligible subjects in the Pilot Stage will be randomised in a 2:1 ratio to achieve 4 active and 2 placebo subjects. In the Primary Study Stage, eligible subjects will be randomised in a 1:1 ratio to the active or placebo arm, using a blocked randomisation scheme with a block size of 6. The randomisation sequence will be based on a computer programme, which will allocate a random number that determines the study drug (GDNF or aCSF) dispensed by the pharmacy whilst maintaining concealment of allocation.

All study drug will be prepared by an unblinded pharmacist at the study site based on the randomisation. Ready to use preparations of GDNF or aCSF will be provided to the PI or designee in identical containers identifiable only by codes unknown to the PI or any other study staff. Drug preparation guidelines are provided in a separate pharmacy manual.

In the event that there is a delay in randomization which results in the baseline assessment occurring more than 24 weeks after screening visit 2, efficacy outcome measures completed during screening but not repeated at baseline must be repeated

prior to the baseline visit unless they have a significant practice effect. The list of measures to be repeated includes:

- Stroop
- Reaction time
- FrSBe
- UPPS-P
- PD NMSS
- PDQ-39
- EQ-5D
- SNAQ
- UPSIT
- QUIP

## **5.6 Schedule of Treatments and Assessments**

Upon receipt of blinded study drug as described above, the PI or designee will initiate a 40-week (approximately 9 months) course of four-weekly intrapatamenal administration of GDNF or placebo via CED. The full course will comprise 11 scheduled visits (baseline and 10 q4 weekly visits). Except for the final visit at Week 40 where no randomised drug infusion will be given, at each visit GDNF/placebo will be administered, followed by clinical assessment of safety, including dyskinesias and falls, mood and impulsivity. If necessary, infusion visits may take place over more than 1 day, for example when study drug infusion is planned for early morning. At Week 40, Primary Study Stage subjects will receive another gadolinium contrast-containing test infusion of diluent, followed both by T1-weighted and by T2-weighted and FLAIR MRI scans. AEs, concomitant medications and vital signs will be recorded at all visits. PD assessments and QUIP will be performed every 8 weeks, and full assessments of safety and PD variables will be performed at baseline and the final assessment.

### **5.6.1 Baseline and First Treatment (Week 0)**

As part of the baseline assessments, all subjects will undergo PET scanning between randomisation and the first infusion with study drug.

The subject will report to the investigative centre (PI or designee) for baseline assessments and to begin treatment.

For this assessment, subjects will withhold all PD medications as follows:

- No PD medications will be taken after 6:00 PM on the night before the Baseline assessments and
- No long-acting PD medications will be taken on the day before the Baseline assessments.

Subjects will refrain from eating any high-protein foods on the morning of the assessments.

At the beginning of the assessment, all OFF period measures are to be completed first:

- UPDRS part II (ADL) and part III (motor) in OFF-state (Section 5.7.1.1)
- Timed walking test (Section 5.7.1.2)
- Timed tapping test (Section 5.7.1.3)

A levodopa challenge will then be performed (refer to study-specific Standard Operating Procedures) and when the subject goes ON the following post-challenge tests will be performed:

- Full UPDRS (including parts I, II, III and IV; Section 5.7.1.1)
- Timed walking test (Section 5.7.1.2)
- Timed tapping test (Section 5.7.1.3)
- QUIP (Section 5.7.2.6)

Additional pretreatment assessments which can be completed irrespective of ON/OFF status will include the following:

- Weight and height.

- Vital signs: Seated systolic and diastolic BP, HR, RR and temperature will be assessed after the subject has been sitting quietly for at least 5 minutes. Standing systolic and diastolic BP and HR will also be assessed after the subject has been standing for 3 minutes.
- Collection of subject PD fluctuation diaries (Section 5.7.1.4)
- Any changes to concomitant medications from the previous visit will be recorded. All over-the-counter or prescription medications, vitamins, and/or herbal supplements will be recorded in the CRF with their indications.
- Any AEs observed or reported since the previous visit will be recorded.

After completion of the pretreatment procedures and assessments, the unblinded pharmacist will provide blinded study drug to the PI or designee, who will administer the drug over a period of approximately 90 to 150 minutes using pre-programmed micro-infusion pumps (detailed in Sections 6.2 and 6.3).

***Pilot Stage subjects:*** The infusion of blinded study drug will be performed in the 3T MRI suite with real-time MR imaging. Rapid acquisition T2-weighted and FLAIR MRI scans will be performed at approximately 20 minute intervals. Real-time MRI scans will be assessed by the PI, Study Neurosurgeon or appropriately experienced designee. Real-time imaging will facilitate immediate cessation of infusions via one or more catheters if any of the following criteria are met:

1. Intraputamenal haemorrhage or post-surgical fluid collection is identified
2. The catheter is blocked
3. There is significant reflux of infusate out of the putamen without evidence of intrapatamenal distribution.

Final T2-weighted and FLAIR 3T MRI scans will be completed within 2 hours of the infusion.

Subjects will be carefully observed for safety during and after study drug administration. During administration, whilst in the scanner, HR, RR and oxygen saturation will be monitored continuously, and systolic and diastolic BP will be collected every 15 minutes. Both seated and standing systolic and diastolic BP and HR will be assessed within 30 minutes after the end of the infusion. A brief neurological

screen (Glasgow Coma Scale) will also be done before infusion, 30 minutes into the infusion, and after completion of the infusion.

Subjects will remain at the facility for safety observation for at least 22 hours (i.e., including an overnight stay) after completing study drug administration.

**Primary Study Stage subjects:** Subjects will be carefully observed for safety during and after study drug administration. During administration, seated vital signs (systolic and diastolic BP, HR and RR) will be collected every 15 minutes, and both seated and standing systolic and diastolic BP and HR will be assessed within 30 minutes after the end of the infusion. A brief neurological screen (Glasgow Coma Scale) will also be done before infusion, 30 minutes into the infusion, and after completion of the infusion.

Subjects will remain at the facility for safety observation for at least 4 to 6 hours after completing study drug administration.

### 5.6.2 Post-Baseline Treatments

After the Baseline assessment and Week 0 treatment, subjects will return to the clinic for repeat treatments every 4 weeks at Weeks 4, 8, 12, 16, 20, 24, 28, 32 and 36. Week 4 must be  $\pm 1$  day of scheduled date; all other treatments may be  $\pm 3$  days. If necessary, in the Primary Study Stage, a treatment may be given a maximum of + 7 days from the scheduled date; if the treatment cannot be given within + 7 days, it will be considered missed and the treatments will resume with the following scheduled date. Before each PD outcome measure assessment (Weeks 8, 16, 24 and 32), subjects will withhold all PD medications and begin the assessments in the OFF state (as detailed in Section 5.6.3). For all other treatments, subjects may take their PD medications as usual and report to the hospital irrespective of whether they are ON or OFF.

At every treatment, the following procedures and assessments will be performed before treatment:

- Vital signs: Seated systolic and diastolic BP, HR, RR and temperature will be assessed after the subject has been sitting quietly for at least 5 minutes. Standing systolic and diastolic BP and HR will also be assessed after the subject has been standing for 3 minutes.

- Any changes to concomitant medications from the previous visit will be recorded. All over-the-counter or prescription medications, vitamins, and/or herbal supplements will be recorded in the CRF with their indications.
- Any AEs observed or reported since the previous visit will be recorded.

After completion of the pretreatment procedures and assessments, the unblinded pharmacist will provide blinded study drug to the PI or designee, who will administer the drug over a period of approximately 90 to 150 minutes using pre-programmed micro-infusion pumps.

Subjects will be carefully observed for safety during and after study drug administration. During administration, seated vital signs (systolic and diastolic BP, HR and RR) will be collected every 30 minutes, and both seated and standing systolic and diastolic BP and HR will be assessed within 30 minutes after the end of the infusion. A brief neurological screen (Glasgow Coma Scale) will also be done before infusion, 30 minutes into the infusion, and after completion of the infusion.

*Pilot Stage subjects only:* Subjects will remain at the facility for safety observation for at least 4 to 6 hours after completing study drug administration at Week 4, for at least 2 to 4 hours after completing administration at Week 8, and for at least 1 to 2 hours after completing study drug administration at all subsequent treatments.

*Primary Study Stage subjects:* Subjects will remain at the facility for safety observation for at least for at least 2 to 4 hours after completing study drug administration at Week 4, and for at least 1 to 2 hours after completing study drug administration at all subsequent treatments.

The last treatment will be administered at Week 36.

At the treatment before each Interim Assessment to assess PD outcome measures and at the last treatment (i.e., at Weeks 4, 12, 20, 28 and 36), subjects will be issued PD fluctuation diaries (Section 5.7.1.4) to complete at home before the next assessment. The subject will be instructed to complete diaries for 3 consecutive predetermined days in the week prior to the next study treatment. The day immediately prior to the study treatment is NOT to be used for diary recording.

### 5.6.3 Interim Assessments

Subjects will undergo extended safety and efficacy assessments every 8 weeks at Weeks 8, 16, 24 and 32.

For these assessments, subjects will withhold all PD medications as follows for assessment in the OFF state:

- No PD medications will be taken after 6:00 PM on the night before the assessments and
- No long-acting PD medications will be taken on the day before the assessments.

Subjects will refrain from eating any high-protein foods on the morning of the assessments.

Interim Assessment visits will also be used to administer treatments, and procedures and assessments will include those listed in Section 5.6.2 for Treatments, but the following assessments will also be performed pretreatment:

At the beginning of the assessment, all OFF period measures are to be completed first:

- UPDRS part II (ADL) and part III (motor) in OFF state (Section 5.7.1.1)
- Timed walking test (Section 5.7.1.2)
- Timed tapping test (Section 5.7.1.3)

A levodopa challenge will then be performed (refer to study-specific Standard Operating Procedures) and when the subject goes ON the following post-challenge tests will be performed:

- Full UPDRS (including parts I, II, III and IV; Section 5.7.1.1)
- Timed walking test (Section 5.7.1.2)
- Timed tapping test (Section 5.7.1.3)
- QUIP (Section 5.7.2.6)

Additional study procedures which can be performed irrespective of ON/OFF state include:

- Collection of subject PD fluctuation diaries (Section 5.7.1.4)

- Weight and height

#### **5.6.4 Laboratory and Other Assessments**

The following laboratory procedures will be performed at Weeks 4, 16, and 28:

- Clinical laboratory tests, including haematology (haematocrit, haemoglobin, MCH, MCHC, MCV, platelet count, RBC, WBC count and WBC differential [basophils, eosinophils, lymphocytes, monocytes and neutrophils]), serum chemistry (albumin, alkaline phosphatase, ALT, creatinine, eGFR, glucose, potassium, sodium, total bilirubin and urea) and urinalysis (colour, appearance, pH, glucose, ketones and nitrite; microscopy only required if indicated to follow up abnormal findings). A pregnancy test will be performed for all women of childbearing potential.
- Blood samples for anti-GDNF antibodies and plasma GDNF levels. The samples will be stored at -70°C until central analysis after all subjects have completed the study.

Subjects will undergo NMSS (Section 5.7.1.5) and RT (Section 5.7.2.4.3) assessments at Weeks 12 and 24.

In subjects randomised in the Pilot Stage, T2-weighted and FLAIR 3T MRI will be completed within 2 hours of completion of the infusions at all post-baseline treatments. In Primary Study Stage subjects, no interim T2-weighted or FLAIR MRI monitoring will be done unless clinically mandated. However, Primary Study Stage subjects will receive another gadolinium contrast-containing test infusion of diluent, followed both by T1-weighted and by T2-weighted and FLAIR MRI scans, at any time within a 2-week window around Week 40.

In subjects randomised in the Pilot Stage, PET will be performed at Week 12. All subjects will undergo PET scanning at any time in the two weeks prior to Week 40.

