## 5.5 Study Procedures

Planned study participation for each subject (both Pilot and Primary Study Stage cohorts) will comprise the following 4 periods:

- Presurgery: Up to 60 days
- Surgery and Healing: Approximately 8 weeks post-surgery (including 4 weeks recovery followed by a test infusion of diluent to confirm catheter function and drug distribution, and a further 4 week-interval before the first infusion of study drug), or longer if needed to meet the post-surgery randomisation criteria.
- Double-blind Treatment: GDNF or placebo infusions every 4 weeks for 9 months; the total dose of GDNF administered at any given infusion will be 240  $\mu$ g (600  $\mu$ L of 0.20  $\mu$ g/ $\mu$ L GDNF per putamen).

Volumetric catheter performance will be determined both by gadolinium contrast-enhanced T1-weighted and by T2-weighted and FLAIR 3T MRI scans throughout the study. The first post-infusion scan will be obtained following the test infusion of artificial CSF (aCSF) (diluent) approximately 4 weeks into the healing period and 4 weeks prior to the first planned infusion of study drug in all subjects. In Pilot Stage subjects, this will be T2-weighted and FLAIR MRI only. In Primary Study Stage subjects, the test infusion will contain 2 mM gadopentetate dimeglumine and be followed by a T1-weighted MRI scan in addition to the T2-weighted and FLAIR MRI scans. Pilot Stage subjects will further undergo post-infusion imaging with all study treatments. In Primary Study Stage subjects, no interim T2-weighted or FLAIR MRI monitoring will be done unless clinically mandated. At Week 40 (where no randomised drug administration is scheduled), Primary Study Stage subjects will receive another gadolinium contrast-containing test infusion of diluent, followed both by T1-weighted and by T2-weighted and FLAIR MRI scans. All post-infusion scans are to be completed within 2 hours following the infusion.

To allow for optimisation of infusion procedures in response to potential surgical, technical, infusion, imaging or logistical issues, Pilot Stage subjects will be receiving the test infusion of aCSF and the first infusion of study medication in the 3T MRI suite with real-time MR imaging. Rapid acquisition T2-weighted and FLAIR MRI scans will be performed at approximately 20 minute intervals during these infusions.

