#### **5.5.2.1 Screening Visit 1**

The first screening visit will occur within 60 days before the planned surgical procedure. After the subject has provided informed consent, the following screening procedures and assessments will be performed in an outpatient clinic setting:

- Demographics (including date of birth, sex and race).
- Full medical history, including PD history, Hoehn and Yahr staging and prior treatments for PD
- Full physical examination, including assessments of body systems. Findings on screening physical examination will be recorded as medical history

- Weight and height
- Supine systolic and diastolic blood pressure (BP), heart rate (HR), respiration rate (RR), and temperature will be assessed after the subject has been resting quietly for at least 5 minutes. Standing systolic and diastolic BP and HR will also be assessed after the subject has been standing for 3 minutes.
- Standard 12-lead electrocardiogram (ECG). At least the following ECG parameters will be recorded: HR, PR, QT, QRS and corrected QT (QTc) intervals. The report will be signed by the PI or designee and will be recorded in the case report form (CRF) whether it is normal, abnormal but not clinically significant, or abnormal AND clinically significant (together with details of the abnormality). In the latter case the eligibility of the participants will be reviewed.
- Clinical laboratory tests, including haematology (haematocrit, haemoglobin, mean cellular haemoglobin [MCH], mean cellular haemoglobin concentration [MCHC], mean cellular volume [MCV], platelet count, red blood cell [RBC] count, white blood cell [WBC] count and WBC differential [basophils, eosinophils, lymphocytes, monocytes and neutrophils]), serum chemistry (albumin, alkaline phosphatase, alanine transaminase [ALT], creatinine, estimated glomerular filtration rate [eGFR], glucose, potassium, sodium, total bilirubin and urea) and urinalysis (colour, appearance, pH, glucose, ketones, nitrite and microscopy). A pregnancy test will be performed for all women of childbearing potential (women not of childbearing potential are those who are surgically sterile or are > 45 years and without menses for  $\geq 2$  years). All laboratory results will be reviewed and the reports signed by the PI or designee for determination of eligibility. Actual values will be recorded in the CRF.

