### 5.5.3 Surgery and Healing

Following completion of screening procedures and assessments, eligible subjects will be consented prior to undergoing any surgical procedures.

Within 60 days of the first screening visit, subjects will report to the North Bristol NHS Trust for implantation of CED catheters (2 in each putamen). All surgical procedures will be carried out according to institutional practices and under the direction of the Study Neurosurgeon. Subjects will remain hospitalised postsurgery for a period of time determined by the Study Neurosurgeon or designee and based on the individual subject's course of recovery. Catheter placement will be assessed by computed tomography (CT).

Subjects will be allowed to heal for approximately 4 weeks after surgery. Data collected during surgery and healing will include concomitant medications and AEs.

After the 4-week healing period, subjects who, in the opinion of the Study Neurosurgeon and PI, have not experienced an unacceptable surgical complication and continue to meet the entry criteria (the healing period may be extended if, in the opinion of the Study Neurosurgeon and PI, such extension is necessary to allow adequate recovery) will undergo an intrapatamenal test infusion of aCSF (diluent) using the infusion algorithm for study medication (detailed in Section 6.3).

***Pilot Stage subjects:*** The test infusion of aCSF will be performed in the 3T MRI suite with real-time MR imaging. Rapid acquisition T2-weighted and FLAIR MRI scans will be performed at approximately 20 minute intervals. Real-time MRI scans will be assessed by the PI, Study Neurosurgeon or appropriately experienced designee. Real-time imaging will facilitate immediate cessation of infusions via one or more catheters if any of the following criteria are met:

1. Intrapatamenal haemorrhage or post-surgical fluid collection is identified
2. The catheter is blocked
3. There is significant reflux of infusate out of the putamen without evidence of intrapatamenal distribution

Subjects will be carefully observed for safety during and after administration of the test infusion. During administration, whilst in the scanner, HR, RR and oxygen saturation will be monitored continuously, and systolic and diastolic BP will be collected every 15 minutes. Both seated and standing systolic and diastolic BP and HR will be assessed within 30 minutes after the end of the infusion. A brief neurological screen (Glasgow

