### 5.8 PET Scanning Procedures and Image Analysis

$^{18}\text{F}$ -DOPA PET will be performed at baseline and 9 months in all randomised subjects. Additional 3-month scans will be obtained from subjects randomised during the Pilot Stage.

For the PET scanning procedure, subjects will withhold all PD medications as follows:

- No PD medications will be taken after 6:00 PM on the night before the procedure and
- No long-acting PD medications will be taken on the day before the procedure.

Subjects will refrain from eating any high-protein foods on the morning of the procedure.

Upon arrival, subjects will receive 150 mg of carbidopa and 400 mg of entacapone (peripheral L-DOPA decarboxylase and catechol-o-methyl transferase inhibitors, respectively). After 1 hour, a low dose CT scan will be acquired (3 s) for attenuation correction and then 111 MBq of  $^{18}\text{F}$ -DOPA in normal saline will be administered as an intravenous bolus at the start of scanning. Using a GE Discovery 690 PET/CT (GE Healthcare; Chalfont St. Giles, UK), dynamic images will be acquired as 26 time-frames over 94.5 min (1 × 30 sec, 4 × 1 min, 3 × 2 min, 3 × 3 min, and 15 × 5 min). The analyses will follow established procedures as described by Nandhagopal et al.

[22]. As a further refinement, co-registered MRI images will be used as a guidance on where to place the regions of interest, rather than just visual inspection.

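### No pregnancy test is scheduled between Screening Visit 1 and Week 4, so the baseline PET/CT and the first infusion rest on a result from before surgery

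*Protocol*

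**What the plan says.** Section 5.5.2.1 places the pre-dose pregnancy test in the Screening Visit 1 laboratory panel and times that visit: "The first screening visit will occur within 60 days before the planned surgical procedure". In Table 1 the laboratory row is marked at Screening Visit 1 only. Inclusion criterion 10 (Section 5.3.2) asks for a negative test at study entry and for contraception until the study ends.

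After surgery come about four weeks of recovery, the test infusion, "and a further 4 week-interval before the first infusion of study drug" (Section 5.5). In that second interval, "all subjects will undergo PET scanning between randomisation and the first infusion with study drug" (Section 5.6.1). The scan uses 111 MBq of 18F-DOPA, and "a low dose CT scan will be acquired (3 s) for attenuation correction" (Section 5.8).

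At Week 0, Section 5.6.1 introduces its last group of checks with "Additional pretreatment assessments which can be completed irrespective of ON/OFF status will include the following" and names weight and height, vital signs, diaries, medications and adverse events. It lists no laboratory or pregnancy test, and the Table 2 laboratory row is blank at Week 0. The next tests follow Section 5.6.4: "The following laboratory procedures will be performed at Weeks 4, 16, and 28". A last one is done at Week 40 (Section 5.6.5).

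Section 5.6 says in summary that "full assessments of safety and PD variables will be performed at baseline and the final assessment".

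**The concern.** Staff who follow Section 5.6.1 and Table 2 exactly would give a radiotracer, a CT scan and a first intracerebral infusion of GDNF on a pregnancy result obtained before surgery. Pregnancy is a listed reason for discontinuation (Section 5.10), and any pregnancy is to be followed for birth defects (Section 7.8), so the protocol treats it as a hazard. A pregnancy that began after screening would be found at Week 4 at the earliest, after exposures that cannot be undone.

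No other clause closes the gap. Before the test infusion, subjects must "have not experienced an unacceptable surgical complication and continue to meet the entry criteria" (Section 5.5.3), and Section 5.5.4 has eligibility confirmed before randomisation, but neither check comes with a new scheduled result. The rescreening rule (Section 5.5.2.3) would repeat the test, but only when surgery itself is late. It does not cover delay after surgery.

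What is at stake is the safety of a small number of subjects. The efficacy comparison is not involved.

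**Working it through.** The check is calendar arithmetic, with day 0 as the day of surgery.

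**Inputs**
- Screening Visit 1: 0 to 60 days before surgery (Section 5.5.2.1).
- Test infusion: about day 28 (Sections 5.5 and 5.5.3).
- First infusion of study drug (Week 0): about four weeks later (Section 5.5).
- Baseline PET: after randomisation and before the first infusion (Section 5.6.1). Section 5.5.3 implies randomisation from about day 28; Table 2 marks it under Week 0.
- Surgery delay tolerated without rescreening: up to 14 days beyond the window (Section 5.5.2.3).
- On-treatment tests: Weeks 4, 16, 28 and 40. Infusions: every 4 weeks, Weeks 0 to 36.

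**The plan's own figure.** 4 + 4 = 8 weeks = 56 days from surgery to first infusion. This agrees with the approximately 8 weeks stated in Section 5.5.

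**Age of the last scheduled result (days)**

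| Event | Calculation | Age |
|---|---|---|
| Test infusion | (0 to 60) + 28 | 28-88 |
| Baseline PET/CT, randomisation from day 28 | (0 to 60) + (28 to 56) | 28-116 |
| Baseline PET/CT, randomisation at Week 0 | (0 to 60) + 56 | 56-116 |
| First infusion | (0 to 60) + 56 | 56-116 |
| First infusion, with surgery tolerance | upper end 60 + 14 + 56 | 130 |
| One extra 4-week cycle | 116 + 28, or 130 + 28 | 144, or 158 |

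The lower ends are slightly optimistic. Diaries are kept on three successive days between the two screening visits, so Screening Visit 1 cannot fall on the day of surgery. The upper ends are not maxima: healing may be extended, and a repeated test infusion or a catheter replacement adds further cycles, with no limit stated.

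Section 5.5.4 itself foresees a baseline more than 24 weeks after Screening Visit 2. In that case the screening result would be older than about 24 × 7 = 168 days.

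**Comparison with later infusions.** If each scheduled result is seen before that day's infusion, the ages are 0 days at Weeks 4, 16 and 28; 28 days at Weeks 8, 20 and 32; and (12 − 4) × 7 = 56 days at Weeks 12, 24 and 36. The oldest is 56 days. The first infusion therefore equals or exceeds this by 56 − 56 = 0 to 116 − 56 = 60 days on the nominal schedule.

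**Week 40 PET.** It may be done in the two weeks before Week 40, so it relies on the Week 28 result: (38 − 28) × 7 = 70 to (40 − 28) × 7 = 84 days.

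**The case against.** The strongest reply is that the protocol already controls the risk. Contraception is required. The age range is 35-75, and women over 45 without menses for two years do not count as of childbearing potential. Eligibility is re-checked twice, and the PI may repeat a test at either check. Hospital practice before surgery may include one. Most of this stands, and it is why few subjects are likely to be affected. It does not supply a scheduled result, however, and a test on the day of surgery would itself be about 56 days old at Week 0.

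A reader might infer from the summary sentence in Section 5.6 that a baseline test was intended and dropped by mistake. The documents do not settle this. Several baselines are openly taken from screening to spare burden, so the sentence may be a loose summary. The gap exists on either reading, because a screening value can serve as a laboratory baseline but does not show current pregnancy status.

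The late-baseline rule in Section 5.5.4 might also be read as having overlooked the pregnancy test. That rule is expressly about efficacy measures, so its silence on a safety test is not a defect. It shows only that long delays are foreseen.

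Finally, a reader might take the 12-week testing interval, 84 days, as the protocol's accepted age, on the ground that results may not be available before the same day's infusion. On that reading the Week 4 infusion too would rest on the screening result, then (56 to 116) + 28 = 84-144 days old. So 84 days would not be the upper limit, and the reading gives no support to the present schedule.

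**Conclusion.** The gap is real, and the protocol does not close it elsewhere. On the nominal schedule the pregnancy result is about 28-116 days old at the baseline PET/CT (56-116 if randomisation is at Week 0) and about 56-116 days old at the first infusion. The upper end is 130 days with the surgery tolerance, and there is no stated limit once healing is extended. If scheduled results are seen before infusion, the first dose has a check no fresher than any later dose, and often an older one.

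The conclusion assumes that the approximate four-week intervals are kept and that no unscheduled test is done. The number of women of childbearing potential is not given, so the number at risk cannot be estimated; contraception and the age range suggest that it is small.

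This is a minor safety point. It would be wrong to infer any weakness in the primary endpoint, the power or the comparison between arms.

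**What to change.** In Sections 5.5.3 and 5.6.1 and in Tables 1 and 2, for women of childbearing potential:

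1. Add a pregnancy test at the test-infusion visit, before the infusion, with the result seen before randomisation.
2. Repeat it before the baseline PET/CT and before the Week 0 infusion; one test serves if both fall on the same day. With step 1 alone, the result would be up to 56 − 28 = 28 days old at either event. With same-day repeats it is 0 days.
3. Repeat it whenever baseline is delayed.
4. If the Week 40 PET is to be covered, add a test before it and keep the Week 40 test. Moving the existing test forward instead could cut the check after the last dose (Week 36) from four weeks to two.

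The cost is two or three quick tests per woman of childbearing potential, around visits that already take place, plus one more if step 4 is adopted. A positive result before randomisation would delay or exclude the subject. A positive result after randomisation would leave an undosed subject in the ITT set, where the margin is 36 − 34 = 2 subjects (Section 8.2). Testing before randomisation limits that risk to a pregnancy first detected in the roughly four weeks before Week 0.
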